### Objective 2: assessment of effects

#### Design and target population

A longitudinal quasi-experimental design will be used. The target population is all workers in cancer care teams in the participating institutions: 240 in the first one (integrated health and social services network) 300 at the second [university hospital], 125 and 30 respectively in the two others (integrated health and social services university networks). The exact number of workers who will be directly impacted by the interventions in each setting will be defined on the basis of the work situation analysis and the action plan developed in the workshops (component 1 of the project).

#### Sample

Workers from the four institutions will be asked to respond to a questionnaire. Even with a conservative response rate of 50% of people answering at all the measurement times, we have calculated that, on the basis of a significance level of 0.05, a power of 80% and an intra-subject correlation of 0.5, our study will be able to detect a standardized difference between two measurement times (d of Cohen) equivalent to 0.26 (institution 1), 0.24 (institution 2), 0.36 (institution 3) and 0.78 (institution 4) standard-deviation units. This corresponds to a low effect size, which is very good, for the first three institutions [48]. The assessment of effects will therefore focus primarily on these first three institutions. For the last one, we will limit ourselves to tests on small sample sizes (e.g.: Wilcoxon test).

#### Variables and instruments

The effects of the intervention will be assessed on the basis of **four dependent variables**: team resilience [37], perceived effectiveness of team [45, 46], well-being at work measured by burnout [44] and absenteeism. In addition to the intervention itself, **the independent variables** considered will be (1) worker resources (personal resources measured by work ability [39]; social network [40]; organizational resources measured in terms of the support of supervisors and peers and decision latitude;) [41] (2) work-related demands (psychological and emotional demands [42] and work-life conflict;) [43] (3) sociodemographic characteristics (age, sex, education, immigration status); (4) job characteristics (job category, status, working hours;) [47] (5) degree of implementation of intervention (level of effective implementation of action plan developed in workshops). To measure this last variable, we will use the method proposed by Steckler and Linnan [49]. It combines two elements: the administered intervention dose (the number of activities conducted in relation to those planned) and the dose actually received (worker participation in the activities). The exact details regarding how these two elements will be measured will be adjusted on the basis of the various action plans.

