## Methods

### Objective 1: implementation

The intervention will involve all the workers who are members of cancer care teams in the participating institutions, including doctors. Team members are divided up into various job categories, each one having its own specific characteristics. However, in this research project, the main focus is on teams and the interdependencies between their members. From this perspective, all job categories will be taken into consideration.

Following the workshops, 2 months will be devoted to preparing for the implementation. In addition to mobilizing resources, preparation will involve two main activities:

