#### Data analysis

The effects of the dependent variables (resilience, perceived effectiveness of team, burnout, absenteeism) will be assessed by means of generalized estimating equation regressions with a non-structured correlation matrix. This type of model is particularly robust and well suited to longitudinal data [50]. It will allow the various measurement times to be analysed simultaneously without imposing unrealistic constraints on the data. Regression models will be constructed for each site and each dependent variable, taking into account the intervention and the other independent variables mentioned above.

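### Degree of implementation sits beside the intervention in each site-specific model, so the intervention coefficient is either not estimable or becomes the change at zero dose

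*Protocol article*

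**What the plan says.** Four statements in Component 2 of the protocol article combine.

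- **Exposure.** Objective 1: "The intervention will involve all the workers who are members of cancer care teams in the participating institutions, including doctors". Under Objective 2, Design and target population: "A longitudinal quasi-experimental design will be used". No comparison group is described.
- **Covariates.** Variables and instruments opens the list of independent variables with "In addition to the intervention itself" and gives as item (5) "degree of implementation of intervention (level of effective implementation of action plan developed in workshops"). This item is built from a site-level and a worker-level part: "the administered intervention dose (the number of activities conducted in relation to those planned) and the dose actually received (worker participation in the activities"). Only the way these are measured is left to be adapted to the action plans.
- **Model.** Data analysis: "Regression models will be constructed for each site and each dependent variable, taking into account the intervention and the other independent variables mentioned above".
- **Timing and target.** T1 falls just before the start, T2 at 6 months and T3 at 12 months. The Sample section justifies the numbers by the detectable difference between two measurement times.

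**The concern.** With everyone at a site covered and a separate model per site, the intervention can differ only between measurement times. Its coefficient is therefore a before/after contrast. Degree of implementation is necessarily zero before the start and positive only afterwards, so it carries much of the same information. With both in one model, the coefficient labelled as the intervention effect may not be identified, or may describe workers or waves with no dose. Objective 2 asks for the effects of the interventions on resilience, well-being, perceived effectiveness and absenteeism, and the sample-size statement concerns the overall change between two times. A site could see a real improvement and report a small, imprecise intervention coefficient because the improvement had moved to the dose term.

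**Working it through.** **1. The plan's own target.** Inputs from the Sample and Design and target population sections: two-sided alpha 0.05 (sidedness assumed), power 80%, intra-subject correlation 0.5, and 50% of 240, 300, 125 and 30 workers.

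d = (1.960 + 0.842) × √(2(1 − 0.5)) / √n. For institution 1, 2.802 / √120 = 0.256.

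The exact paired-t version gives 0.258, 0.230, 0.359–0.362 and 0.778, against the stated 0.26, 0.24, 0.36 and 0.78. Institution 2 comes to 0.23, so the stated figure is slightly cautious; this has no bearing here. The figures reproduce as a simple paired difference between two times, with no dose term.

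**2. Identifiability within one site.** Let administered dose be 0 at T1, d2 at T2 and d3 at T3, the same for all workers at the site. Then dose = d2·1(T2) + d3·1(T3). Adding T0 changes nothing, since dose is zero there too.

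| Columns besides the intercept | Rank / columns | Result |
|---|---|---|
| T2 and T3 indicators + administered dose | 3 / 4 | aliased |
| Pre/post + administered dose, equal at T2 and T3 | 2 / 3 | aliased |
| Pre/post + administered dose 0, 0.6, 0.9 | 3 / 3 | estimable; intervention term is the change extrapolated to zero dose |
| T2 and T3 indicators + worker-level received dose | 4 / 4 | estimable; time terms are the change at zero participation |

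**3. How much moves to the dose term.** With a pre/post indicator (coefficient a) and administered dose (coefficient b), the changes are a + b·d2 at T2 and a + b·d3 at T3. Assume doses 0.45 and 0.90:

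| Assumed change at T2, T3 (SD) | b | a |
|---|---|---|
| 0.15, 0.30 | 0.15/0.45 = 0.33 | 0.15 − 0.15 = 0 |
| 0.25, 0.30 | 0.05/0.45 = 0.11 | 0.25 − 0.05 = 0.20 |
| 0.30, 0.30 | 0 | 0.30 |

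**4. Simulation.** Assumptions: n = 120, three waves, correlation 0.5, administered dose 0/0.6/0.9, participation varying between workers, mean post-start change 0.30 SD proportional to received dose, 300 runs. An exchangeable working correlation was used; the plan names an unstructured one.

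| Model | Mean intervention coefficient | SE | Rejected |
|---|---|---|---|
| No dose term | 0.30 | 0.08 | 96% |
| + administered dose | −0.02 | 0.22 | 4% |
| + received dose | 0.00 | 0.14 | 5% |
| + received dose, centred among post-start records | 0.30 | 0.08 | 96% |

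The near-zero means follow from assuming proportionality. The loss of precision with administered dose does not. With wave means m1, m2, m3, b = (m3 − m2)/0.3 and a = m2 − m1 − 0.6b = 3·m2 − m1 − 2·m3. Its SE is √(0.5 × (9 + 1 + 4)/120) = 0.24, close to the simulated 0.22, whatever the shape of the effect. Without dose it is √(0.5 × (1 + ½)/120) = 0.08.

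At 80% power, SEs of 0.14 and 0.22 correspond to detectable values of 2.80 × 0.14 = 0.39 and 2.80 × 0.22 = 0.62 SD, against the stated 0.26 for institution 1.

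**The case against.** **Not all of the variable is a function of time.** A reader might infer that degree of implementation is aliased in every form. It is not: participation varies between workers, and a measure that includes it is not a combination of wave indicators. Strict aliasing needs administered dose as its own column, in the first two codings above. Software would normally flag it. This stands and limits the aliasing claim; the zero-dose interpretation remains for the other codings.

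**One value per wave is an assumption.** The number of workers directly affected is to be settled later, and activities could differ between teams within a site. Administered dose would then vary between workers, and the change at zero dose would be partly observed. This stands too, but it would still be a different quantity from the overall change.

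**Coding may be settled in an analysis plan not shown.** Centring dose among post-start records, entering it as a worker-constant covariate or moving it to a secondary model would each remove the problem. However, the article leaves open only how dose is measured. Its place beside the intervention in each model is stated, and none of these remedies is.

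**Total loss of the effect.** A reader might infer that the intervention would be reported as having no effect. That follows only if the effect is proportional to dose, and a positive dose coefficient would itself suggest an effect.

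**Causal reading and self-selection.** Nothing in the article says the dose coefficient will be read causally, or that healthier or less loaded workers attend more. Work ability, job category, working hours and demands are already listed as covariates. What remains is that participation is not assigned.

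**Conclusion.** The point holds as one about model specification. As written, each site-specific model contains both the intervention and its degree of implementation, and the intervention coefficient then does not estimate the overall pre-to-post change that the sample size is based on and Objective 2 needs. Depending on coding, it is either aliased with administered dose or is the change at zero dose.

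The size cannot be fixed from the article. The share of the effect that moves to the dose term runs from none to all, according to how closely the effect tracks dose. In the illustration, the standard error rises from 0.08 to 0.14–0.22. The doses, effects and participation pattern are assumptions, as is a single administered dose per site and wave. The conclusion also rests on no comparison group being described and on dose being zero before the start. It concerns mainly the first three institutions, since the fourth is limited to small-sample tests.

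**What to change.** - Omit degree of implementation from the main effect models. State that the intervention effect is the T1-to-T2 and T1-to-T3 contrast for all workers, regardless of participation. For absenteeism, use the corresponding before/after contrast in the administrative data.
- Analyse received dose in a separate secondary dose-response model, with the covariates already listed plus baseline burnout. Label it associational, because participation is not assigned.
- Report administered dose descriptively, by site and wave.

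The cost is a change of wording and one extra secondary model. No additional data are needed.

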#### Data collection

The strategy will include:
*A repeated questionnaire*: To be completed just before the start of the intervention (**T1**), 6 months after the start of the intervention (**T2**, all activities will have begun) and at 12 months (**T3**, full impact of intervention). The questionnaire will be the same one that was used for component 1 of the project (**T0**) and will cover all the aforementioned variables except absences.*Collection of administrative data* on hours worked and absences, covering 12 months before the intervention and up to 12 months after the start of the intervention.

#### Data analysis

The effects of the dependent variables (resilience, perceived effectiveness of team, burnout, absenteeism) will be assessed by means of generalized estimating equation regressions with a non-structured correlation matrix. This type of model is particularly robust and well suited to longitudinal data [50]. It will allow the various measurement times to be analysed simultaneously without imposing unrealistic constraints on the data. Regression models will be constructed for each site and each dependent variable, taking into account the intervention and the other independent variables mentioned above.

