### Objective 3: economic assessment

#### Design

A cost-benefit assessment will be conducted, as it is particularly well suited for assessing the cost-effectiveness of an intervention [51]. The assessment will compare the costs and consequences of the intervention with the costs and consequences of doing nothing, based on the following time references: the 12 months preceding the start of the intervention and the 12 months following the implementation of all the activities provided for in the action plans. The analysis will take into account the trends observed during the year.

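### The absenteeism model is given covariates that come mainly from the questionnaire, so an outcome taken from administrative records depends on survey response unless those covariates are dropped or imputed.

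*Protocol article*

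**What the plan says.** Absenteeism is one of four dependent variables; under Variables and instruments the last two are "well-being at work measured by burnout [44] and absenteeism".

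Under Objective 2, Data collection, absenteeism has its own source: administrative data "on hours worked and absences, covering 12 months before the intervention and up to 12 months after the start of the intervention". The repeated questionnaire "will cover all the aforementioned variables except absences".

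The independent variables, besides the intervention, include "personal resources measured by work ability [39]; social network [40]; organizational resources measured in terms of the support of supervisors and peers and decision latitude", work-related demands, work-life conflict, sociodemographic and job characteristics, and degree of implementation. The last combines the dose delivered with the dose received, meaning each worker's participation in the activities.

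Data analysis then applies one approach to all outcomes: "The effects of the dependent variables (resilience, perceived effectiveness of team, burnout, absenteeism) will be assessed by means of generalized estimating equation regressions". On the content of the models it adds: "Regression models will be constructed for each site and each dependent variable, taking into account the intervention and the other independent variables mentioned above". No separate model is described for absenteeism.

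The Sample section plans on this basis: "Even with a conservative response rate of 50% of people answering at all the measurement times". Institution 4, with 30 workers, is assigned small-sample tests, so the regression matters mainly for the first three institutions.

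**The concern.** A shared covariate list suits the three survey outcomes, because a worker who supplies the outcome supplies the covariates on the same form. Absenteeism is different. Its data do not require anyone to fill in a form, but the model does. A regression row without its covariates cannot be used, so the absence analysis inherits the survey's non-response.

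Three things are at stake:

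- **Precision.** Workers with absence data but no questionnaire contribute nothing.
- **Selection.** A worker on leave when a questionnaire goes out is plausibly less likely to answer. Entry into the model, or the loss of a wave, can then depend on the outcome. Ordinary unweighted GEE does not protect against that.
- **Adjustment for a consequence of the outcome.** Workers who are absent cannot attend activities. Dose received is therefore partly determined by absence, and its coefficient would look protective even if the activities did nothing.

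**Working it through.** **Step 1. Match each variable to its source.**

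- Absence and hours worked: administrative data (Objective 2, Data collection).
- Work ability, social network, support, decision latitude, demands, work-life conflict: questionnaire, with no administrative source named.
- Age, sex, job category, status, working hours: also on the questionnaire, though an HR department may hold them. The article does not say.
- Dose received: worker participation, with measurement details left to each action plan.

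Six constructs on the list therefore tie the absence model to questionnaire response.

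**Step 2. Reproduce the plan's detectable differences, to see how the 50% is used.** Inputs from the Sample section: alpha 0.05 (taken as two-sided; the article does not say), power 80%, within-subject correlation 0.5. For a paired comparison of two times, the SD of the difference is √(2(1 − 0.5)) = 1 SD unit. Solving for 80% power with the noncentral t at half of each roster:

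| Institution | Workers | n at 50% | Computed | Stated |
|---|---|---|---|---|
| 1 | 240 | 120 | 0.258 | 0.26 |
| 2 | 300 | 150 | 0.230 | 0.24 |
| 3 | 125 | 62 or 63 | 0.362 or 0.359 | 0.36 |
| 4 | 30 | 15 | 0.778 | 0.78 |

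Three of four agree. A stated 0.24 fits n of about 133 to 144 rather than 150. That gap is small, on the cautious side, and does not bear on this point. The plan's precision is thus that of workers who answer every time.

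**Step 3. Count the workers.** 240 + 300 + 125 + 30 = 695. Half is 347.5, about 348 with complete data. Standard error ratio against the whole roster: √(695/347.5) = √2 ≈ 1.41. For institutions 1 to 3 alone, 665 workers and 332.5 at 50%, the ratio is the same.

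GEE keeps the completed waves of partial respondents, so 1.41 is an upper bound at the planned response rate. If the usable information were 70% or 80% of the whole (assumed values), the ratio would be 1/√0.70 = 1.20 or 1/√0.80 = 1.12.

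**Step 4. What the whole roster would give.** The calculation in Step 2 with n = 240, 300, 125 and 30 gives detectable differences of about 0.18, 0.16, 0.25 and 0.53. This is illustrative: it assumes individual absence records for all workers and treats absence as a continuous paired outcome.

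**Step 5. Why selection could matter.** The article gives no absence figures, so these are assumptions: 120 absence days for a worker on long leave and 8 for any other. With a share p on long leave, their share of all absence days is 120p / (120p + 8(1 − p)):

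- p = 2%: 2.4 / 10.24 = 23%
- p = 5%: 6 / 13.6 = 44%
- p = 10%: 12 / 19.2 = 63%

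These are ceilings on what could be lost. T1, T2 and T3 are six months apart, so a leave shorter than that overlaps at most one of them. Such a worker may answer the other two. The wave at risk, however, is the one that falls during the leave.

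**The case against.** The strongest reply is that the article never limits the absence analysis to respondents. Handling of missing covariates is commonly left to an analysis plan, which is not shown, and the wording on independent variables leaves room to omit some. Baseline values alone might be used, and the T0 survey collects the same variables. This stands to a degree: the exclusion is the default result of the model described, not a stated rule, and the lack of an imputation method is not a fault here. What remains is that this document does choose the covariate list for each dependent variable, and the choice does not suit absenteeism. Imputation would have to supply six questionnaire constructs for up to half the roster, with response possibly related to the outcome.

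Three stronger readings are tempting, and the document does not support them.

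- A reader might infer that HR holds an absence record for every worker. The Component 1 description of administrative data speaks of groups of workers, and the level of the Objective 2 data is not stated. Individual records are an inference, although a model with age, sex and job covariates seems to need them.
- A reader might infer that the cost-benefit inputs lose the long absences too. Objective 3, Data collection, takes the consequences from HR administrative data, and nothing ties them to questionnaire response.
- A reader might infer that any secular trend would be credited to the intervention, since the economic design is to "compare the costs and consequences of the intervention with the costs and consequences of doing nothing" and its Analysis section compares with the previous year. The same Design section says that trends observed during the year will be taken into account. The method is not given, but the intention is.

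**Conclusion.** The point holds as a mismatch between an outcome from administrative records and a covariate list drawn largely from the questionnaire. As written, the absenteeism regression depends on survey response, and one of its covariates is affected by absence.

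In size, about 348 of 695 workers would have complete data at the planned 50%, with standard errors up to about 1.4 times those of a whole-roster analysis. The bound rests on that response rate; partial respondents reduce the loss, and actual response below 50% would increase it. It also assumes that administrative records cover the whole roster.

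Selection related to absence is plausible, but the article gives nothing from which to estimate its size or direction. If the same kind of worker were missing at every wave, the before-after change would be distorted less than the level. The matter is worth correcting before analysis and does not undermine the survey outcomes.

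**What to change.** In Objective 2, Data analysis, state a separate main model for absenteeism:

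- Include all target-population workers with administrative records, whether or not they answered the questionnaire.
- Analyse absence hours relative to scheduled or contracted hours where HR holds them.
- Adjust only for covariates held administratively, such as age, sex, job category, status and hours. Leave dose received out.
- Model the pre-start trend from the 12 months of administrative data already planned. Implementation takes six months, so let the effect build up rather than assume only a step at the start.
- If HR supplies grouped data only, fit the model at group-by-month level.
- Keep the model with questionnaire covariates as secondary, in respondents, and label it so.

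**Cost:** a change of wording, a little more analysis work, and less covariate adjustment in the main absence model. The data are those already planned, provided that HR can supply them by month. One pre-start year supports only a simple trend, and its last six months (four of workshops plus two of preparation) overlap with co-construction. An absence series from non-oncology units would add a concurrent comparison, but it needs new data and is optional.

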### Theoretical framework

The project will be based on a theoretical body of work incorporating two perspectives: resources theories and theories of empowerment.

***Resources theories*** (demands-resources model, conservation of resources, job decision latitude) focus on the complexity of the determinants associated with mental health problems at work and the processes for developing resilience [23–25]. From this perspective, resilience depends on various personal (e.g.: stress management skills), social (e.g.: social network) and organizational (e.g.: support from supervisor) resources that teams can mobilize in hazardous situations. These resources can play a role as a buffer and provide protection against excessive demands or hazardous situations [26]. One characteristic of resilient teams is their ability to build a capacity pool and to tap into it when facing adverse situations [27, 28]. In situations where a loss of resources is inevitable, resilient teams stand out by their ability to control the management of these losses (redefine objectives, reallocate remaining resources to priority activities, review strategies and means available) and build new resources and capacity [29]. These theories will be useful, in this project, to help guide the construction of interventions in support of the development of various types of resources (personal, social, organizational) and to ensure balance with the demands teams must deal with.

***Theories of empowerment*** focus on the roles of the players involved in resilience development processes [30–32]. Contrary to top-down paternalist approaches, theories of empowerment take into account abilities that workers themselves can develop in conjunction with their employers to create more suitable work environments [33]. What make these theories particularly relevant is their holistic viewpoint that encompasses the ecology of the interventions, that is, the many factors that influence the problems and various perspectives of stakeholders [34]. They thus provide inspiration for an interactive approach that relies on multiple social and organizational mechanisms to foster intense interaction between the groups involved in the co-construction of the interventions [35].

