### Component 2: intervention implementation and assessment

#### Objectives

While component 1 will identify the priority problems and develop an action plan for addressing them (first type of ability in intervention framework), component 2 will directly concern the second and third types of abilities: *ability to respond to hazardous situations* by implementing co-constructed interventions and *ability to learn from difficult situations that arise*.

Three objectives are targeted: (1) Implement the intervention continuums developed by and specific to each of the four institutions; (2) Assess the effects of the interventions on team resilience, well-being, perceived effectiveness and absenteeism; (3) Assess the cost-benefit ratio of the interventions.

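### The effect models list worker resources and work demands, which the interventions aim to change, as covariates without limiting them to pre-intervention values, so the intervention coefficient may be only a partial effect

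*Protocol article*

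**What the plan says.** All references are to the protocol article.

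- **Target.** Under Component 2, Objectives, the second aim is "Assess the effects of the interventions on team resilience, well-being, perceived effectiveness and absenteeism". No direct effect and no mediation aim is stated.
- **Covariates.** Variables and instruments counts decision latitude among the resources and lists, besides the intervention, "worker resources (personal resources measured by work ability [39]; social network [40]; organizational resources measured in terms of the support of supervisors and peers". The demands on the list are "work-related demands (psychological and emotional demands [42] and work-life conflict". It also holds sociodemographic and job characteristics and, last, "degree of implementation of intervention (level of effective implementation of action plan developed in workshops".
- **Timing.** Under Objective 2, Data collection, the questionnaire is given at T1 (just before the start), T2 (6 months) and T3 (12 months). It is the instrument already used at T0, and it "will cover all the aforementioned variables except absences".
- **Model.** Data analysis specifies GEE regressions with an unstructured correlation matrix, all measurement times analysed together, one model per site and outcome, "taking into account the intervention and the other independent variables mentioned above".
- **Mechanism.** The Theoretical framework says the resources theories will "help guide the construction of interventions in support of the development of various types of resources (personal, social, organizational"), and will help keep those resources in balance with the demands on teams. Table 1 includes workshops on managing stress and demand.

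**The concern.** A variable that the intervention is meant to move, and that is measured after the start, lies on the path from intervention to outcome. If its current value sits beside the intervention term, the intervention coefficient no longer answers the stated objective. It gives only the part of the effect that bypasses that variable. The better an intervention builds resources, the more of its benefit is credited to the covariates. This would affect all four outcomes at the three institutions on which the effect assessment concentrates. The detectable differences in the Sample section describe a plain difference between two times, so they do not describe the power of such a model.

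**Working it through.** **1. The plan's own figures.** Inputs from the Sample and target population sections: alpha 0.05 (taken as two-sided, since the article does not say), power 80%, intra-subject correlation 0.5, and 50% response from populations of 240, 300, 125 and 30. The SD of a within-person change is √(2(1 − 0.5)) = 1 SD. The normal approximation to the detectable difference is (1.960 + 0.842)/√n; the noncentral t refines it.

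| Institution | n | Normal | Noncentral t | Stated |
|---|---|---|---|---|
| 1 | 120 | 0.256 | 0.258 | 0.26 |
| 2 | 150 | 0.229 | 0.230 | 0.24 |
| 3 | 62–63 | 0.356–0.353 | 0.362–0.359 | 0.36 |
| 4 | 15 | 0.723 | 0.778 | 0.78 |

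Three of the four reproduce. Institution 2 gives 0.23, so the stated 0.24 is slightly conservative. This has no bearing on the present point.

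**2. What adjustment removes.** Let the total effect be d, with a share m passing through one resource M. Write M = a·T + noise and Y = d(1 − m)·T + b·M + noise, with a·b = d·m. Without M, the coefficient on T is d(1 − m) + a·b = d. With current M in the model, it is d(1 − m). For d = 0.26:

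- m = 0.25: 0.26 × 0.75 = 0.195
- m = 0.50: 0.26 × 0.50 = 0.130
- m = 0.75: 0.26 × 0.25 = 0.065

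**3. Paired-t power for the remaining effect**, starting from each institution's stated detectable difference and ignoring any precision gained from the covariates:

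| Institution | m = 0 | 0.25 | 0.50 | 0.75 |
|---|---|---|---|---|
| 1 (n = 120) | 80.7% | 56.3% | 29.2% | 10.5% |
| 2 (n = 150) | 83.2% | 59.1% | 30.9% | 10.9% |
| 3 (n = 62) | 79.7% | 55.3% | 28.6% | 10.3% |

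**4. GEE simulation for institution 1.** Settings: n = 120, three waves, intervention indicator 0 at T1 and 1 at T2 and T3, true total effect 0.26 SD, one continuous mediator with b = 0.5, 200 replicates per row. The working correlation was exchangeable, where the plan specifies unstructured. Each cell gives the mean estimate and the rejection rate.

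| m | No M | M at T1 only | Current-wave M |
|---|---|---|---|
| 0 | 0.259; 90.5% | 0.259; 90.5% | 0.263; 96.5% |
| 0.25 | 0.256; 90.5% | 0.256; 90.5% | 0.192; 78.5% |
| 0.50 | 0.263; 92.5% | 0.263; 92.5% | 0.132; 48.5% |
| 0.75 | 0.262; 94.5% | 0.262; 94.5% | 0.066; 14.0% |

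The current-wave estimates agree with step 2. Power starts above 80% because two post-start waves are pooled. With nothing mediated, current-wave adjustment does no harm and gains some precision. The first two columns are identical: when everyone responds at every wave, a baseline main effect leaves a within-site before/after contrast unchanged.

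**5. Which values enter the model?** The text does not say outright. Three features favour current-wave values. All waves are modelled together with no baseline restriction. The covariate list contains degree of implementation, which exists only after the start, so the list as a whole is not baseline-only. And, as step 4 shows, baseline main effects would do almost nothing to the contrast being estimated.

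**The case against.** The strongest reply is that the article never says current-wave values are used. Re-measurement proves little, because the same questionnaire also collects age, sex and education again, and covariate timing is often left to a fuller plan. It is right that the time-varying reading is an inference, and with T1 values the loss does not arise. But the point is not that a detail is missing. The article states what goes into every effect model, and that list, read as it stands, conflicts with the objective.

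A reader might infer that all these covariates are mediators. The documents do not support that. The Literature review ties emotional demands partly to the nature of cancer care and treats work-life balance as an individual factor. The Theoretical framework also gives resources a buffering role, which is moderation. Table 1 has nothing aimed specifically at work-family conflict, and each site's activities are unknown until its workshops are held. Supervisor and peer support are plausible mediators; the case is weaker for some of the others.

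The last reply has real force. No control group is described, so demands may shift for outside reasons, and current-wave adjustment is one way to allow for that. It cannot, however, tell an external shift from one produced by the intervention, and it removes both.

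**Conclusion.** The point holds in this form: the model as written admits post-start values of variables that the interventions are built to change, so on its natural reading the intervention coefficient is a partial effect and not the effect named in the objective. The proportional attenuation equals the mediated share. That share is not in the documents, and the 25%, 50% and 75% used here are assumptions. At institution 1 they turn a true 0.26 SD into about 0.19, 0.13 and 0.07 SD; if nothing is mediated, nothing is lost. The illustration uses one continuous mediator and does not represent absenteeism, which comes from administrative records. Simulated power carries a Monte Carlo standard error of up to about 3.5 points (√(0.5 × 0.5/200)).

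A reader might go further and conclude that a successful intervention will appear null. That would need a large mediated share, which the documents neither state nor allow one to estimate.

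**What to change.** - **Main effect models.** Enter resources and demands only at pre-intervention values, together with sociodemographic and job characteristics. T1 is the natural choice, being just before the start. T0 is preferable if co-construction counts as part of the intervention, since Component 1 expects the workshops themselves to build the first type of ability; staff who join after T0 would then have no value. State which is used and why.
- **Degree of implementation.** Move it to a separate dose-response analysis.
- **T2 and T3 resources and demands.** Report them as intermediate outcomes, and present the current-wave-adjusted model as a labelled secondary mediation and sensitivity analysis.

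This changes analysis wording only and needs no new data. Its price should be stated: the main before/after contrast is no longer adjusted for external changes in demands over time. The secondary model can explore such changes but cannot separate them from mediated ones.
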